## Abstract

**Background:**

The world has high hopes of vaccination against COVID-19 to protect the population, boost economies and return to normal life. Vaccination programmes are being rolled out in high income countries, but the pandemic continues to progress in many low-and middle-income countries (LMICs) despite implementation of strict hygiene measures. We aim to present a comprehensive research protocol that will generate epidemiological, sociological and anthropological data about the COVID-19 epidemic in Burkina Faso, a landlocked country in West Africa with scarce resources.

**Methods:**

We will perform a multidisciplinary research using mixed methods in the two main cities in Burkina Faso (Ouagadougou and Bobo-Dioulasso). Data will be collected in the general population and in COVID-19 patients, caregivers and health care professionals in reference care centers: (i) to determine cumulative incidence of SARS-CoV-2 infection in the Burkinabe population using blood samples collected from randomly selected households according to the WHO-recommended protocol; (ii) develop a score to predict severe complications of COVID-19 in persons infected with SARS-CoV-2 using retrospective and prospective data; (iii) perform semi-structured interviews and direct observation on site, to describe and analyze the healthcare pathways and experiences of patients with COVID-19 attending reference care centers, and to identify the perceptions, acceptability and application of preventive strategies among the population.

**Discussion:**

This study will generate comprehensive data that will contribute to improving COVID-19 response strategies in Burkina Faso. The lessons learned from the management of this epidemic may serve as examples to the country authorities to better design preventive strategies in the case of future epidemics or pandemics.

The protocol was approved by the Ministry for Health (N° 2020-00952/MS/CAB/INSP/CM) and the Health Research Ethics Committee in Burkina Faso (N° 2020-8-140).

**Supplementary Information:**

The online version contains supplementary material available at 10.1186/s12879-021-06543-4.

## Background

In late 2019, clusters of infection with a novel coronavirus began to appear in China, often progressing to fatal pneumonia [1, 2]. The infections were due to a highly contagious virus identified on 9 January 2020, called Severe Acute Respiratory Syndrome Coronavirus 2 (SARS-CoV-2), and the associated disease was termed COVID-19 (Coronavirus Disease 2019) [3]. Within a few short weeks, the infection went from a localized epidemic to a worldwide pandemic [4] with more than a million persons contaminated in over 209 countries, and more than 80,000 deaths by 9 April 2020, i.e., only 100 days after notification of the first case [5]. In April 2020, Burkina Faso was experiencing a rapid increase in the number of cases and deaths and ranked as the fifth most affected country in Africa [6, 7], even though the first cases had only appeared one month earlier, and several weeks after the first cases reported in Europe. Epidemic cycles with emergent or re-emergent diseases, combined with endemic diseases, put considerable strain on the health system of Burkina Faso.

Research on COVID-19 has been intensifying around the world [8–12], with numerous ongoing randomized trials including the “Discovery” trial [13] initiated by the European Union, or the “Solidarity” trial, initiated by the WHO [14]. Preliminary results from this latter trial indicate that treatment regimens using remdesivir, hydroxychloroquine, lopinavir/ritonavir, and interferon unfortunately do not appear to be effective in terms of 28-day mortality or the course of disease in hospitalized patients [14]. In Burkina Faso, therapeutic trials are also ongoing [15], notably the CHLORAZ study, which is an observational study comparing the effect of a combination of hydroxychloroquine plus azithromycin (HCQ-AZ) versus the combination of chloroquine phosphate plus azithromycin (CQ-AZ) for the treatment of COVID-19.

However, the greatest hopes for vanquishing this pandemic lie in the development of vaccines, and several countries in Europe and North America have already approved vaccines and commenced population-level immunization. Vaccines already approved and in use include the Pfizer-BioNTech [16], Astra Zeneca [17], Janssen COVID-19 [18], and Moderna mRNA-1273 [19] vaccines. However, with limited financial and infrastructural resources, it remains uncertain whether countries like Burkina Faso will be able to procure and distribute COVID-19 vaccines for the entire population. Therefore, they must focus more than ever on non-pharmacological measures, namely handwashing, masks, physical distancing, curfews, and closure of schools and businesses. Yet, these measures are sometimes difficult to implement and require socio-anthropological information to better orient prevention strategies. In this paper, we aim to present a comprehensive research protocol that will generate epidemiological, sociological, and anthropological data about the COVID-19 epidemic in Burkina Faso, a country where resources are scarce.

Since March 2020, Burkina Faso has been implementing a strategic plan to fight against the epidemic that consists primarily in management of persons with suspected or confirmed SARS-CoV-2 infection with a view to limiting the spread of disease. The plan has contributed to containing the epidemic thus far, but numerous aspects of patient management and prevention of this novel disease remain unexplored and could help to guide public policy and enable the health system to deal more effectively with increases in cases.

Firstly, current techniques for COVID-19 diagnosis are expensive (e.g., PCR, for detection of genetic material from the virus) [20, 21], limiting the number of analyses that can be performed. This makes it difficult, not to say impossible to estimate the actual number of persons infected by the virus in the general population of Burkina Faso. Furthermore, the full spectrum of disease, and the relative proportions of benign or asymptomatic cases not requiring medical care, remain unclear [22]. As in many low- and middle-income countries, in Burkina Faso, the management of the pandemic has concentrated primarily on patients presenting with severe forms of disease. Although recommended by the WHO, few countries have assessed seroprevalence at the population level. According to available studies, seroprevalence for SARS-CoV-2 infection among the general population remains low (below 10%) [22] and reports mainly stem from western countries. In this context, in Burkina Faso, and in Africa in general, there remains some uncertainty as to the principal epidemiological and serological features of this novel pathogen, in particular its capacity to spread among the population, and its virulence. Yet, surveillance of seropositivity for IgG and IgM antibodies [23, 24] would make it possible to detect the spread of infection and estimate the cumulative incidence in the population [22]. It would also give insights during the pandemic into the proportion of the population already exposed to the virus, and thus, potentially immunized.

To the best of our knowledge, scores to predict patients at risk of severe forms of disease, or death, from among those with COVID-19 are not currently available in Burkina Faso or other countries with limited resources. Such scores would make it possible to focus preventive strategies and available resources on this high-risk sector of the population. Such scores might also contribute to reducing the costs associated with management of COVID-19 patients in a country where resources are scarce. To date, few studies have investigated the creation of a score or algorithm for predicting the occurrence of severe complications in patients with COVID-19 [25, 26], especially in African populations where the incidence rate and mortality are lower than the alarmist forecasts of international health authorities at the beginning of the pandemic.

Finally, preventive strategies against COVID-19 were developed and rapidly disseminated to the Burkinabe population by the media, associations, non-governmental organizations, local elected officials, religious and cultural leaders, and healthcare professionals, without giving a second thought to the acceptability of the measures being promoted for the population. However, the literature as well as media reports indicate that during other epidemics, notably Ebola [27–30], the implementation of preventive strategies (including raising awareness among the population, institutional isolation of infected individuals, collective management of cadavers by specialized healthcare teams) led to misunderstanding and conflictual interpretations between national or international scientific experts, and local populations. This breakdown in communication led to increased mortality, underlining the importance of evaluating the acceptability of preventive strategies for the population in the specific context of Burkina Faso. In addition, several specialists have questioned the feasibility of social distancing and isolation of suspected infected individuals in African populations where the community-based culture prevails. There are also unanswered questions regarding the pathways of care, patient management, and patients’ experiences. The specific objectives of this project comprise three phases, namely:To determine cumulative incidence (i.e., seroprevalence) of SARS-CoV-2 infection in the Burkinabe population (phase 1: sero-epidemiological study);To identify the predictors of the occurrence of severe complications and to identify the prognostic factors for mortality (phase 2: clinical epidemiology);To analyze the healthcare pathways and patient experiences of management of COVID-19 in healthcare centers dedicated to SARS-CoV-2 infected patients, and to explore the perceptions, acceptability, and application of preventive strategies among the population (phase 3: socio-anthropological study).

Embracing all these problems, we developed the present project, whose overarching aim is to generate novel, pragmatic epidemiological and socio-anthropological data using robust scientific methods, to support Burkina Faso and guide policy in its fight against the COVID-19 pandemic.

To the best of our knowledge, this will be one of the first studies of this type to be performed in Sub-Saharan Africa since the emergence of COVID-19.

## Methods

### The design and setting of the study

This will be a multidisciplinary study using mixed methods (i.e., combining quantitative and qualitative methods), in three distinct parts, detailed in Fig. 1. Each part of the study is presented separately.

**Fig. 1 Fig1:**
[figure not shown]
The three phases of a multidisciplinary research on COVID-19 in Burkina Faso

It will be conducted in 2021 in Ouagadougou and Bobo Dioulasso, the two main cities of Burkina Faso, a landlocked country in West Africa.

## Phase 1: Sero-epidemiological study

For the investigation of seroprevalence, the protocol recommended by the WHO for sero-epidemiological studies in the general population will be followed [7].

### The characteristics of participants

A longitudinal cohort will be constituted from among the general population in the cities of Ouagadougou and Bobo-Dioulasso (Burkina Faso), which are the hardest hit by the pandemic. Households and persons will be randomly selected, with stratification by age group (60 and over, 19–59 years old, teenagers aged 15–18 and those aged 10–14 years) and gender (male, female) and included in the study. Random selection of the households will be performed based on census units of the national statistics institute of Burkina Faso. A household is considered as at least two persons living in the same dwelling, to consider so-called “celibatoriums”, which are grouped premises comprising several individual lodgings. In each household, all the members of the household will be invited to participate in the study, to collect data at days 0, 21, 42 and 63, to enable analysis by subgroup (age and gender).

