### Inclusion criteria

Published statistics to date regarding COVID-19 in Burkina Faso indicate that there are very few cases in persons under 10 years of age.

The inclusion criteria for the study are as follows:Age 10 years or older.Resident in a census unit of the cities of Ouagadougou or Bobo-Dioulasso that is selected for participation in the study, based on data from the national statistics institute of Burkina Faso.Provide written informed consent.

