After selection of the EAs, the selection of individuals (second degree), will be done as follows:Complete a census and numbering of all concessions (can include several households), all households and target persons (men and women aged 60 and over, women aged 19–59, men aged 19–59, teenagers aged 15–18 and children aged 10–14 years),Number (from 1 to n) all the targeted residents by category,From each category, 28 residents will then be selected among adults and 14 teenagers from every EA.

If a selected participant is unavailable or refuses to participate in the study, he/she will be replaced with an individual randomly chosen from the same age and gender group in the same EA and in the same city. If the number of participants to select cannot be reached in an EA, it will be completed with the subsequent individuals in the randomization list. This strategy allows implicit stratification and is easy to perform. It simply requires that the sampling frame be sorted geographically before sampling systematically, with a probability to be selected proportional to the size. It also automatically provides a sample that is proportionally distributed among geographic subdivisions in the study area. Furthermore, it will make it easier to find the respondents in the field, since the interviewers will already be in touch with them through the census. Sample collection of teenagers will start at round three, enabling field investigators to obtain parental consent for their children to participate in the study during the first two rounds of data collection.

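### The Phase 1 household definition leaves out one-person dwellings, in conflict with the eligibility rule and the person listing; if it governs the listing, eligible residents living alone cannot be selected

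*Protocol article*

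**What the plan says.** All references are to Phase 1 of the protocol article.

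- **The characteristics of participants** defines the unit: "A household is considered as at least two persons living in the same dwelling". The sentence goes on to give a reason: "to consider so-called “celibatoriums”, which are grouped premises comprising several individual lodgings". The same section says "Random selection of the households will be performed based on census units of the national statistics institute of Burkina Faso" and that in each household "all the members of the household will be invited to participate in the study".
- **Inclusion criteria** sets eligibility by age (10 or over), consent and residence: "Resident in a census unit of the cities of Ouagadougou or Bobo-Dioulasso that is selected for participation in the study". There is no condition on household size, and **Non-inclusion criteria** does not mention people living alone.
- **Study endpoints** makes the primary endpoint the proportion of the population with specific antibodies.
- **Sample size calculation** describes the second stage of sampling in each EA: "Complete a census and numbering of all concessions (can include several households), all households and target persons", then "Number (from 1 to n) all the targeted residents by category", then a draw of individuals: "28 residents will then be selected among adults and 14 teenagers from every EA".

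**The concern.** A person living alone is eligible and belongs to the population whose seroprevalence is the primary endpoint, but does not form a household under the stated definition. An enumerator who applies that definition during the EA census has no household to record for that person.

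If such people are left off the list, their selection probability is zero. A larger sample does not shrink the resulting error, and weighting cannot restore people who could never be drawn. Living alone also removes exposure within the household and is likely to be unevenly spread over the age and gender groups, so the subgroup proportions could be affected to different degrees.

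**Working it through.** **1. Does any reading of the definition cover everyone who is eligible?**

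| Reading of a celibatorium | Lone occupant of a lodging | Person alone in an ordinary dwelling |
|---|---|---|
| Each lodging is a dwelling | Not a household | Not a household |
| The whole block is one dwelling | Covered | Not a household |

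The first reading defeats the stated reason for the definition. The second serves it, but still leaves out the person alone in an ordinary dwelling. Neither matches the residence-based eligibility rule.

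**2. Which unit is sampled?** The participant section draws households and invites all members. The sample size section numbers residents by category and draws individuals. Under the first description the definition decides who can be selected. Under the second it matters only if enumerators list persons through households.

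**3. The plan's own figures.** With p = 0.10, d = 0.03 and a two-sided alpha of 5%:

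- n = 1.96² × 0.10 × 0.90 / 0.03² = 384, as stated.
- 384 / 0.85 = 451.8, rounded to 452, as stated.

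Neither figure depends on whether one-person dwellings count as households.

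**4. Possible size of the bias.** Let P be the true proportion, s the share of the eligible population living alone, and r the seroprevalence of people living alone divided by that of people in shared dwellings. A survey that misses people living alone estimates the proportion in shared dwellings, P / [(1 − s) + s·r]. The bias is therefore

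bias = P / [(1 − s) + s·r] − P.

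P = 10% is the planning value in the sample size section. The documents give neither s nor r, so both are assumptions here. Bias in percentage points:

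| s | r = 0.5 | r = 1 | r = 1.5 |
|---|---|---|---|
| 2% | +0.10 | 0 | -0.10 |
| 5% | +0.26 | 0 | -0.24 |
| 10% | +0.53 | 0 | -0.48 |
| 20% | +1.11 | 0 | -0.91 |

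For example, s = 20% and r = 0.5 gives 10 / 0.90 − 10 = +1.11. With r = 1.5 it gives 10 / 1.10 − 10 = -0.91.

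**5. What would it take to reach the planned ±3 points?** Setting the estimate to 13% gives s = (1 − 10/13) / (1 − r). That is 46% living alone at r = 0.5, and 23% even at r = 0.

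**6. A check on s.** Table 2 gives 0.15 + 1.26 + 1.10 + 0.51 + 0.61 = 3.63 persons aged 10 or over per household. If that average includes one-person households, s = 20% over the whole population would need 0.20 × 3.63 = 73% of households to hold one such person. The upper rows of the table are therefore more credible for a single adult stratum than for the population proportion.

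**The case against.** A reader might infer that the plan excludes people living alone and so overstates seroprevalence. The documents do not support either step.

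*Exclusion.* No passage says that people living alone go unlisted. The second stage names target persons alongside households and numbers all targeted residents, and the inclusion criteria admit them. The celibatorium clause suggests that the authors wanted single lodgers in. This stands: zero chance of selection follows only if the household definition governs the listing. It does not remove the conflict, because the participant section says that households are the randomly selected unit, and no reading of the clause reaches a person alone in an ordinary dwelling.

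*Direction.* Less exposure within the household makes a lower seroprevalence among people living alone plausible, but the documents contain nothing on seroprevalence by household size. The sign is set entirely by the assumed ratio.

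*Size.* Every value in the table lies inside the ±3 points planned per stratum, and few people aged 10–18 can be expected to live alone. This also stands, with one qualification. Pooling five strata of 384 at the plan's design effect of 1, unweighted, gives 1.96 × √(0.09 / 1920) = ±1.3 points. A pooled bias of 0.5 points would be more than a third of that, but it needs about 10% of the whole population living alone at r = 0.5.

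*Detail left to a field manual.* An article may well leave listing instructions to a manual. Here, however, the article states a rule, and that rule conflicts with its own eligibility criteria.

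**Conclusion.** The point holds as an inconsistency with a possible coverage bias. The household definition, taken with random selection of households, leaves people living alone outside the sampling unit. The inclusion criteria and the numbering of all targeted residents point the other way. If the definition governs the EA listing, people alone in ordinary dwellings cannot be selected, nor can lone celibatorium occupants where each lodging counts as a dwelling, and the primary endpoint is under-covered.

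Neither size nor direction can be derived from the documents. The range of about -0.9 to +1.1 points rests on a true value of 10%, assumed shares living alone of 2–20%, and assumed seroprevalence ratios of 0.5–1.5. The bias is upward only for ratios below 1. The likely effect is modest, but it cannot be repaired after fieldwork, so the text should be corrected beforehand.

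**What to change.** In the section on participant characteristics, define a household as one or more persons sharing a dwelling, and state how lodgings in a celibatorium are listed, for example each occupied lodging as its own household. Then reconcile that section with the second-stage description under the sample size calculation. Say whether households or individual residents are drawn, and state that residents living alone are listed and numbered within their age and gender category like everyone else.

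The cost is slightly more listing time and some call-backs to one-person dwellings. The figures of 384 and 452 per stratum stay as they are.

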### Inclusion criteria

Published statistics to date regarding COVID-19 in Burkina Faso indicate that there are very few cases in persons under 10 years of age.

The inclusion criteria for the study are as follows:Age 10 years or older.Resident in a census unit of the cities of Ouagadougou or Bobo-Dioulasso that is selected for participation in the study, based on data from the national statistics institute of Burkina Faso.Provide written informed consent.

### Non-inclusion criteria

Persons aged 10 years or over from within the selected zones in Ouagadougou and Bobo-Dioulasso who refuse to participate in the study;Persons under legal guardianship or tutorship or other form of legal protection.

### Study endpoints

The primary endpoint will be the proportion of the population with specific antibodies against SARS-CoV-2.

Secondary endpoints will be as follows:The proportion of the population with specific antibodies against SARS-CoV-2 in each subgroup of age (60 and over, 19–59 years old, teenagers aged 15–18 and those aged 10–14 years) and by gender (males, females).The proportion of asymptomatic infections (presence of antibodies in patients with no clinical signs of SARS-CoV-2 infection) in the population, in each subgroup of age (60 and over, 19–59 years old, teenagers aged 15–18 and those aged 10–14 years) and by gender (males, females).

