### Data collection and management

Data collection in the general population will take place at four timepoints, each 21 ± 3 days apart. Blood samples will be drawn by trained and qualified personnel. In each household, the members of the household who accepted to participate will be invited to sign the informed consent form, and complete a questionnaire (Additional file 1) with socio-demographic data, comorbidities, symptoms related to SARS-CoV-2 infection and exposure, namely:Socio-demographic characteristics: age, profession, marital status, level of education, socio-professional category;Prior medical history:History of cardiovascular and thrombo-embolic disease: arterial hypertension, rhythm disturbances, cardiomyopathy, deep venous thrombosis, pulmonary embolism;History of metabolic diseases: diabetes mellitus, kidney failure;History of pulmonary disease: tuberculosis, asthma, chronic obstructive pulmonary disease (COPD);Other relevant medical history.Lifestyle habits: tobacco and alcohol consumption;Clinical signs of COVID-19: fever (temperature ≥ 38 °C), cough, dyspnea, etc.;Exposure to COVID-19: any contact with a confirmed case of COVID-19.

Persons who complete the questionnaire will be requested to give a blood sample to extract serum for the assessment of SARS-CoV-2 antibodies. Venous blood samples will be collected at the four different timepoints (Days 0, 21, 42, 63) to enable analysis in the laboratory. Blood will be collected by venous puncture performed by health workers within the participant’s home. In total, 4 ml of blood will be drawn in a 5 ml EDTA tube for each participant, at each timepoint.

The blood samples will be transported to the laboratory within 6 h of the collection, along with the relevant follow-up sheet for the blood samples. For transport to the laboratory, blood samples will be triple packed in an isotherm container containing an icebox to preserve the cold chain.

All blood samples will be analyzed in the Laboratory of the MURAZ center in Bobo-Dioulasso. Laboratory procedures involving handling of blood samples will be performed in a class 2 biosafety cabinet. For blood samples collected in the city of Bobo-Dioulasso, samples will be sent to the laboratory daily. Samples from Ouagadougou will also be sent daily to the laboratory of the national center for research and training on malaria in the same city where they will treated.

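### Phase 1 reads antibodies as infection and has no rule for vaccinated participants, so vaccination during 2021 could inflate cumulative incidence and the asymptomatic proportion

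*Protocol article*

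**What the plan says.** **Infection is read from antibodies.** The specific objectives in the Background include "To determine cumulative incidence (i.e., seroprevalence) of SARS-CoV-2 infection in the Burkinabe population". Phase 1, Statistical analysis, then calculates cumulative incidence by age and by gender as the proportion seropositive.

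**Asymptomatic infection is defined the same way.** Phase 1, Study endpoints, lists as a secondary endpoint "The proportion of asymptomatic infections (presence of antibodies in patients with no clinical signs of SARS-CoV-2 infection) in the population", overall and by age group and gender. The primary endpoint in that section is worded differently: it is the proportion of the population with specific antibodies.

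**The test.** Phase 1, Data collection and management, specifies a qualitative total-antibody ELISA and takes a positive result as a sign of recent or prior infection. The target antigen is not stated. Local validation uses 10 PCR-positive and 10 PCR-negative samples; samples from vaccinated people are not mentioned.

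**Timing.** Under Fig. 1: "It will be conducted in 2021 in Ouagadougou and Bobo Dioulasso". The Background names four vaccines already approved and in use, and says "it remains uncertain whether countries like Burkina Faso will be able to procure and distribute COVID-19 vaccines for the entire population".

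**Where vaccination could have appeared.** The inclusion criteria are age, residence and consent ("Age 10 years or older.Resident in a census unit of the cities of Ouagadougou or Bobo-Dioulasso"). The non-inclusion criteria are refusal and "Persons under legal guardianship or tutorship or other form of legal protection". Participants will "complete a questionnaire (Additional file 1) with socio-demographic data, comorbidities, symptoms related to SARS-CoV-2 infection and exposure"; the itemised list that follows also covers medical history and lifestyle, and does not name vaccination.

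**The concern.** The article fixes a classification rule under which any antibody-positive person counts towards cumulative incidence, and any antibody-positive person without clinical signs counts as an asymptomatic infection. The rule is safe only while infection is the sole source of detectable antibodies. In 2021 that cannot be taken for granted: the authors express doubt about vaccine supply for the whole population, which leaves partial coverage open.

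Three results would be exposed. The overall level of cumulative incidence and the asymptomatic proportion would be too high. Comparisons between age groups would be distorted if vaccination reached the groups unevenly. Any rollout between day 0 and day 63 would look like new infection between rounds. This is bias, so a larger sample does not reduce it. A first analysis goes to the authorities after the day 0 collection, and the results are meant to guide policy.

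**Working it through.** **Inputs from the article (Phase 1, Sample size calculation):** expected seroprevalence p = 10%, precision d = ±3 points, alpha 5%, design effect 1, about 85% usable data.

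**Inputs that are assumptions:** v, the share of participants vaccinated, and s, the share of uninfected vaccinees who test positive. The article gives neither, so both are shown as ranges. Vaccination is taken as independent of past infection, and the test as otherwise error-free.

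**Step 1. The plan's own figure.** n = 1.96² × 0.10 × 0.90 / 0.03² ≈ 384, as stated; 384 / 0.85 = 451.8, so 452, as stated. The ±3-point margin therefore corresponds to 384 usable persons per stratum. The present point does not touch this arithmetic.

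**Step 2. Excess in cumulative incidence.** Observed proportion = p + (1 − p) × v × s, so the excess is 0.9 × v × s.

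| v | Observed (excess), s = 0.9 | Observed (excess), s = 1 | Vaccine-only share of positives, s = 1 |
|---|---|---|---|
| 0% | 10.0% (0) | 10.0% (0) | 0% |
| 1% | 10.8% (0.81 points) | 10.9% (0.9 points) | 8% |
| 2% | 11.6% (1.62) | 11.8% (1.8) | 15% |
| 5% | 14.1% (4.05) | 14.5% (4.5) | 31% |
| 10% | 18.1% (8.1) | 19.0% (9.0) | 47% |

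If the assay does not detect vaccine-induced antibodies, s = 0 and the excess is zero at every coverage.

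**Step 3. Coverage at which the excess equals the planned margin.** 3 / 0.9 = 3.3% for s = 1; 3 / 0.81 = 3.7% for s = 0.9.

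**Step 4. Asymptomatic proportion.** Let a be the true asymptomatic share of infections and c the share of vaccine-only positives with no clinical signs (both assumed). Among positives, the apparent asymptomatic share is (0.10 × a + 0.9 × v × s × c) / (0.10 + 0.9 × v × s). With v = 5% and s = 1:

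- a = 50%, c = 100%: (0.050 + 0.045) / 0.145 = 66%.
- a = 50%, c = 80%: (0.050 + 0.036) / 0.145 = 59%.
- a = 80%, c = 80%: (0.080 + 0.036) / 0.145 = 80%, no change.

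If the denominator is the whole population instead, the excess is 0.9 × v × s × c. At v = 5%, s = 1 and c = 100%, a true 5.0% (a = 50%) becomes 9.5%.

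**Step 5. Precision lost by restricting to unvaccinated participants.** With 384 usable persons, the half-width at 10% becomes 3.00 / √(1 − v): 3.08 points at v = 5%, 3.16 at 10% and 3.35 at 20%. These losses are small beside the biases in Step 2.

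**The case against.** **The questionnaire may already ask.** Additional file 1 is not shown, and the article's list has an open category for other medical history. A reader might infer that vaccination is not collected and that the error could never be corrected afterwards. The document does not establish either. What stands is that no stated endpoint or analysis says how such an item would be used.

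**The primary endpoint is not wrong.** A reader might infer that it counts vaccinees as infected. As worded it is the proportion with antibodies, and a vaccinated seropositive person belongs there. The misclassification lies in the objective, the cumulative-incidence analyses and the asymptomatic endpoint.

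**Vaccination of participants is not shown.** The article places rollout in high-income countries, doubts local supply, and gives no coverage, start date or priority group. Nothing indicates that the two strata aged 10 to 18 would be vaccinated. This stands, and it makes the point conditional. Doubt about supplying everyone still does not exclude supplying some.

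**Assay reactivity is unknown.** This also stands: without the target antigen, the document cannot show that vaccinees would test positive.

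**Vaccine-only positives need not be mostly asymptomatic.** That would require them to report none of the listed signs (fever, cough, dyspnea and others), which the document cannot show. The last case among positives in Step 4 shows no shift at all.

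**The analysis is meant to adapt.** Phase 1, Statistical analysis, promises a dynamic approach that takes up new knowledge. That leaves room to add a rule but is not one, and it helps only if vaccination status is recorded at the visits.

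**Conclusion.** The point holds in conditional form. The article states a rule that would misclassify vaccinated, uninfected, antibody-positive people, in a study fielded when partial vaccination was possible by its own account. The quantities at risk are cumulative incidence and the asymptomatic proportion; antibody prevalence as the primary endpoint is unaffected.

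The size depends on two unknowns, coverage and assay response to vaccination. If either is zero there is no bias. Otherwise, for s between 0.9 and 1, low single-digit coverage is enough to match the whole planned margin. The effect on the asymptomatic proportion also depends on how many vaccine-only positives report no signs. The documents do not support saying that the bias will occur, that most of it falls on the asymptomatic endpoint, or that it could not be repaired. A correction is worth making because the rule is explicit and the remedy is cheap.

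**What to change.** 1. Make sure vaccination status, with product and dates, is recorded at each of the four rounds. If Additional file 1 already does this, say so in the data collection section; if not, add the item.
2. Keep the primary endpoint as antibody prevalence in all participants, and describe it as such rather than as infection.
3. Define cumulative incidence and the asymptomatic proportion in participants unvaccinated at the time of sampling, and add a sensitivity analysis that includes vaccinated people.
4. State the target antigen of the ELISA, so that a reader can judge whether vaccine-induced antibodies would be detected.

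**Cost.** At most one short questionnaire item per visit and a sentence or two in the endpoint and analysis sections. If vaccination does occur, the infection estimates rest on a smaller denominator, with the modest loss of precision shown in Step 5, and more in any stratum where vaccination concentrates. Unvaccinated participants may also be less representative of the general population, so the restricted estimates should be labelled accordingly and read beside the sensitivity analysis. If nobody is vaccinated, the estimates do not change.
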